## DATA MONITORING AND SAFETY

A data and safety monitoring board is not considered necessary since all the interventions in the Package are based on current international guidelines and have been proven to be both effective and safe. The salt substitute and low salt diet have also been shown by our own or other’s previous studies as effective and safe.

A data safety and monitoring plan will be established. The safety of study participants will mainly be assured by having expert consultation available to the village doctors and by monitoring digitized case management records. Village doctors will receive clear instructions to refer patients to hospital-based doctors or specialists, whenever necessary. Both emergency and non-emergency referrals are included in the training. The county cardiologist who will train the village doctors will be available for consultation should such needs arise. The case management records taken by the village doctors in the intervention villages will be digitized and uploaded to a central database on a bi-monthly interval. These records will be regularly reviewed by study cardiologists to detect any abnormal patterns including adverse effects and medically appropriate actions will be taken when necessary.

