**3) Men ≥50 years old, or women ≥60 years old, who have systolic blood pressures ≥160mmHg on at least 2 occasions.**

This record is required to be filled out for all of the above high-risk patients. It is not required for other patients.

1. It is required to fill out the follow-up record every month for all the high-risk patients for cardiovascular diseases. If they come to the office more than once in a month, extra records need to be filled out ONLY when changes in treatments are made.
2. Please make sure to record it in “Chief Complaints,” when high-risk patients for cardiovascular diseases visit the office with emergencies.
3. Please make sure to answer all questions with “**□**” by marking “**√**” in appropriate “**□**”. Otherwise, the record is considered incomplete and will not quality for payment.
4. Please make sure to answer all the questions with “ ” by filling out with appropriate information. Otherwise, the CMR is considered incomplete and will not quality for payment.

Thanks for your cooperation!

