**Chief Complaints**

| **New Conditions and Medication Use** |
| --- |
| 1. From the last visit to the present, did the patient have any one of the following diseases diagnosed (in county or higher-level hospitals)？   **CAD**□Yes□No; **Hemorrhagic stroke**□Yes□No; **DM**□Yes□No; **Ischemic stroke**□Yes□No |
| 1. From the last visit to the present, has the patient been trying to？   **Reduce salt intake** □Yes □No; **Quit smoking** □Yes □No; **Avoid binge drinking** □Yes □No  **Be physical active** □Yes □No **Control weight** □Yes □No; |
| 1. Medications the patient was taking everyday ≥25 days in the past month (please record the **name**, **dosage** taken each time, and **times** taken each day, e.g. “Hydrochlorothiazide 12.5mg qd”; if no medication meets the above criteria, please record “NA”): |
| **Physical Examination** |
| 1. Blood Pressure (SBP/DBP): / mmHg 2. Weight: kg; other signs: |
| **Prescription** |
| 1. Referral □Yes □No |
| 1. Therapeutic lifestyle changes (advise the patient to take actions to):   **Reduce salt intake** □Yes □No; **Quit smoking** □Yes □No; **Avoid binge drinking** □Yes □No  **Be physical active** □Yes □No **Control weight** □Yes □No; |
| 1. Pharmaceutical treatment (please record the **name** of the drug, **dosage** taken each time, and **times** taken each day, e.g. “Hydrochlorothiazide 12.5mg qd”; if no drug is prescribed, please record “NA”):   Doctor’s Signature: |
| **(Optional: the following questions to be asked every 6 months)**   1. Does the patient take measures to reduce dietary sodium aggressively in everyday life?   □Yes (e.g. do not eat pickled vegetables at all; no MSG and add minimal amount of salt when cooking dishes; unable to eat when the meal is salty.)  □Not so aggressively (e.g. eat some pickled vegetables; take care to reduce salt added in cooking; eat less when the meal is salty.)  □No (e.g. do not pay attention to the amount of salt in food at all.)   1. Is the patient a current smoker？ □Yes □No   If “Yes”, does the patient think about quitting smoking？ □Yes □No   1. Does the patient exercise regularly？(e.g. farming, walking, climbing, etc.)   □Almost everyday □3-5 time/week □1-2 times/week □almost no activities/week |

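### The case management record is the protocol's tool for detecting adverse effects, but its follow-up page does not ask about side effects, all-cause hospital admission or why a drug was stopped

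*Protocol*

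**What the plan says.** The section DATA MONITORING AND SAFETY considers a data and safety monitoring board unnecessary and states what takes its place: "The safety of study participants will mainly be assured by having expert consultation available to the village doctors and by monitoring digitized case management records". On the use of the records it adds: "These records will be regularly reviewed by study cardiologists to detect any abnormal patterns including adverse effects". It also announces a further document: "A data safety and monitoring plan will be established".

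The record is in Appendix 1-B. On the follow-up page, the only structured question about new illness begins "From the last visit to the present, did the patient have any one of the following diseases diagnosed" and offers coronary disease, hemorrhagic stroke, ischemic stroke and diabetes. Drug use is recorded as "Medications the patient was taking everyday ≥25 days in the past month", with NA if no drug qualifies. The page also has Chief Complaints, blood pressure, weight, a free-text space for other signs, a referral box, lifestyle advice, and the drugs prescribed at that visit with dosage and frequency.

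The instructions at the front of the record require one follow-up record a month. For further visits in the same month, "extra records need to be filled out ONLY when changes in treatments are made". The next instruction says that Chief Complaints must be filled in "when high-risk patients for cardiovascular diseases visit the office with emergencies".

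**The concern.** A review can find reliably only what the form collects. Here the protocol gives the detection of adverse effects to readers of a form that does not ask about them. The form asks about drug use, lifestyle and four diagnoses in a structured way, and leaves harm to whatever the village doctor happens to write as free text.

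At stake is the quality of one of the two main safeguards for managed patients. According to the informed consent section, these patients are not asked for individual consent. If few adverse effects appear in the records, the reviewing cardiologists cannot tell whether few occurred or whether nobody asked.

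**Working it through.** There is no figure to reproduce. The check compares the stated purpose with the content of the form and its recording rules.

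**Step 1: what the follow-up page can show (Appendix 1-B, Follow-up Visits).**

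| Needed to recognize an adverse effect | Field on the page |
| --- | --- |
| Side effect since last visit | None; only free text in Chief Complaints or other signs |
| Hospital admission for any cause | None |
| Drug stopped or changed | Not asked; inferable from prescription and medication items |
| Reason for the stop or change | None |
| Low blood pressure | Yes, the reading at the visit |
| Referral | Yes or no, without a reason field |
| New coronary disease, stroke or diabetes | Yes |

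**Step 2: the medication item.** The threshold is "everyday ≥25 days in the past month". Take a drug prescribed in one record:
- Taken for 5 days and then stopped: absent from the next list of drugs taken.
- Taken irregularly on 20 days: also absent.
- Never started: also absent.
- Taken for 26 days and then stopped: still listed as taken.

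Because each page also lists what was prescribed, the reviewer can see in the first three cases that a prescribed drug was not taken as intended. The page does not separate the three or give the reason, whether intolerance, cost, supply or improved blood pressure. The last reason is realistic here. The protocol's account of its pilot work reports more withdrawal from medication with salt substitute, and 30 of the 60 package townships also receive the salt program.

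**Step 3: which visits produce a record (Appendix 1-B, instructions).**

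| Visit | Record required? |
| --- | --- |
| Monthly visit | Yes |
| Extra visit, treatment changed | Yes |
| Extra visit for a suspected side effect, no treatment change | No |
| Extra visit ending in non-emergency referral, no treatment change | No |
| Extra emergency visit, no treatment change | No by one instruction, yes by the next |

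The last row is the conflict to reconcile.

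**Step 4: whether another instrument fills the gap.**
- The mortality and morbidity surveillance system covers deaths and cardiovascular events. A non-fatal fall, or a bleed outside the brain, is out of scope. The protocol does not link this system to the cardiologists' review.
- The population survey (Appendix 2, item D.2) asks only about hospital stays for heart disease, stroke, diabetes or hypertension and has no side-effect item. It also uses independent random samples, so it does not follow the managed patients.
- The section on amendments and additional submissions lists components still to come. It names surveillance and audits of the records, but neither the content of the record nor the safety plan.

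**Step 5: scope.** The record is used in the 60 package villages, for an estimated 10,000 patients, with at most 12 × 2 = 24 monthly records per patient over two years. This is the number of people under the review, not an estimate of missed events.

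**The case against.** The form is not blind. Chief Complaints and other signs can hold any symptom, blood pressure is taken at each visit, and referrals and prescriptions are recorded. A visit at which the doctor changes a drug because of a side effect must be recorded. A symptom raised at an unrecorded visit can be written down at the next monthly one. Cardiologists also give on-site consultation at least twice a year. The form is called a sample, and a safety plan is still to be established. The review is described as leading to medical action, and no adverse-effect outcome is listed, so it is not presented as evidence of safety. All of this stands, and it limits the point.

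For the same reasons, several stronger readings that a reader might infer are not supported:
- That the review cannot see adverse effects at all. The fields above give partial sight.
- That stopped drugs vanish from the record. The prescription item lets a stop be inferred; what is lost is the reason.
- That every drug stopped early is entered as NA. NA is used only if no drug at all meets the threshold.
- That most extra visits go unrecorded. The protocol gives no visit counts.
- That deaths are lost because the booklet has no field for them. All village doctors must report deaths through the surveillance system.

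On the two instructions about extra visits, one can read the emergency rule as an exception to the general one. That is plausible, but the general rule is worded as exclusive, and village doctors should not have to choose between them.

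The objection does not supply a question about side effects or about the reason for a stop. The announced safety plan might, but the only review of records that the protocol describes is the reading of these pages.

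**Conclusion.** The point holds in a limited form. The safety section promises detection of adverse effects from a record whose follow-up page has no structured item for side effects, for admission of any cause, or for the reason a drug was stopped or changed. Some unscheduled visits need no record, and for emergencies without a treatment change the instructions conflict. Detection is therefore indirect and depends on what each village doctor chooses to write.

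The weakness affects the safety review in the 60 package villages, not the blood pressure outcomes, which come from the surveys. Its effect in missed adverse effects cannot be estimated, because the protocol gives neither adverse-effect rates nor visit counts. The conclusion assumes that the sample form is close to the one to be printed and that the safety plan adds no separate collection of side effects. It is an improvement worth making before printing, not a fault that undermines the trial.

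**What to change.** Before the booklet is printed:

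1. Add three items to the follow-up page of Appendix 1-B: side effect since the last visit (yes or no, specify); hospital admission for any cause since the last visit (yes or no, specify); and any drug stopped or changed since the last visit, which one and why.
2. Reword the instruction on extra visits so that a same-month visit for an emergency, a referral or a suspected side effect also produces a record. This reconciles it with the instruction on emergencies.
3. Name these fields in DATA MONITORING AND SAFETY as what the cardiologists review.

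The instructions already make an unticked box a ground for withholding payment, so yes-or-no items should be answered more consistently than free text. The change concerns data collection only and alters no treatment rule. It costs slightly longer visits, a few more database fields and brief extra training, with no additional staff or procedures.

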# PROJECT TIMELINE

The two interventions will be implemented at two different stages with the package intervention starting first according to the following schedule and the salt reduction about 6 months later due to practical concerns of the complexity of starting two interventions at the same time.

- May 2010 - July 2010: ethics Committee submissions and approvals
- May 2010 – August 2010: development of standard operating procedures
- September 2010 –October 2010: baseline surveys and training the trainers
- October 2010 – October 2012: intervention
- November 2012 to Jan 2013: follow-up surveys
- February 2013: study close-out and final evaluation survey
- March 2013 – May 2014: data cleaning, analysis, and report writing

# ETHICS REVIEW AND HUMAN SUBJECT PROTECTION

The project will be reviewed by the Ethics Committee of the Peking University Health Science Center in Beijing, China and the Duke University Health System Institutional Review Board, USA. Ethic review will also be conducted by the National Heart, Lung, and Blood Institute, USA.

### Human subject protection certification and training

All collaborating organizations have received the FWA (Federal-Wide Assurance) from the US Department of Health and Human Services Office of Human Research Protections. All study personnels have received or will receive either on-line or in-person trainings on human subject protections and obtain the CITI certificate before they begin the study.

### Participant informed consent

Participant consent for this project has particular challenges because of the community level nature of the intervention and the requirement to obtain community consent in addition to the usual individual consent. The study team will work with our local collaborators to first introduce the study to the provincial bureau of health. After obtaining their support and consent, we will introduce the study to the county department of health to seek their support and input on the selection of townships in their county to participate in the study. The consent process at each level will be similar: First, an initial group presentation and discussion of the project will be conducted. This will be followed by time for reflection and the opportunity for each stakeholder group to consult with the research team individually as required. A final decision to participate, or not, will be made at a second face-to-face meeting of the parties with the final decision provided to the researchers in writing at the county levels.

Individual consent of participants in the surveys will be done in the usual way. Participant information sheet and consent form for the village doctors are in Appendix 4-A; for survey participants in Appendix 4-B.

There will be an estimated 10,000 high-risk patients to be managed in 2 years in 60 villages. No individually identifiable information in the case management records will be collected or digitized by study personnel. Only the first page of the case management records has individually identifiable information. Such information will be entered by the village doctors and can be viewable by only the village doctors and the study monitor digitizing such paper-based data. All high-risk patients in the package intervention group will be identified by a unique study ID. Patient records transmitted to the Data Management Centre will be identified only by a unique number and date of birth; in other words, no individually identifiable information such as name, address, or personal ID will be included in the digitized database. Therefore, there is no need to obtain informed consents from high-risk patients being managed by the village doctors as part of their enhanced clinical practices.

### Participant risks and benefits

Two types of interventions are proposed: package and salt reduction. No or minimal risks will be imposed by the community education intervention (using means of public announcement system, flyers, and town hall meetings etc.) or by usual care planned for the control group. The package intervention will follow standardized guidelines for the identification and treatment of patients with high cardiovascular risks such as hypertension and cardiovascular diseases. These drugs (such as diuretics and aspirin) have been used in the market for many years and have been proven to be safe in most patients. Adequate trainings will be provided to the village doctors who prescribe these drugs. Outcome assessments will involve a simple set of questions, basic anthropometry, a blood pressure measurement and a 24hr urine collection. No or minimal risks will be imposed by these measurements.

A potential risk to the participant is the inadvertent release of his/her information obtained during the course of the study. This possibility is minimized by having computer-readable data records for statistical analyses identified only by code number and maintaining names, addresses, and other identifying information used in the study (when such information is collected such as in the surveys) in separate databases on secure servers with password protection. Paper records and other identifying information are maintained separately in locked files. and all project personnel (including the data management team) will sign data confidentiality agreement and will be thoroughly indoctrinated in maintaining confidentiality of data. All data collected in this study will be kept strictly confidential with access granted to only authorized personnel. No report or manuscript will contain any information that would allow an individual participant in the study to be identified.

Benefits to individual participants include opportunity to have current cardiovascular risk factors evaluated at no cost, and treatments when needed for the package intervention group, and free education for the community education group. More importantly, results of the proposed study, with small or no risk to individual participants, may have important implications for public health policy and allocation of resources for chronic disease prevention and control in rural China, where low-cost, effective, and sustainable strategies are urgently needed. Thus, potential problems in this research are few, low order, and potential benefits very great.

### Inclusion of women, minorities, and children

There will be equal efforts to enroll men and women; thus by design the survey sample will be drawn to include approximately 50% women. The study will be conducted in 5 regions in Northern China where our 5 local partners are located. One of the regions is in Ningxia Hui People Autonomous Region where a lot of Hui minority people reside. More than 30% of the participants in this region, over 6% of overall sample, will belong to the Hui minority group. There are very few minorities living in the other 4 regions and will result in only small numbers of minorities being recruited into the sample there. The participants in the project will primarily be adults since it is adults that mostly suffer from hypertension and chronic diseases; hence, the topic is not relevant to children and none are to be included. However, the community education intervention aimed at all villagers in the same village may benefit children as well.

### Amendments and additional submissions

Amendments to the protocol, participant information sheet or consent form will be submitted to the ethics committee for approval. Such amendments will only be implemented once ethical approval has been obtained, unless an amendment is being made to eliminate immediate hazards to study participants, which is highly unlikely in this study.

Certain components of this study are not determined at this time or will be informed by the results of the initial phase of the study; thus are not available in this protocol. These include details on

- The salt reduction intervention
- Process evaluation
- Economic evaluation
- Morbidity and mortality surveillance
- Procedures to conduct quality audit of the case management records
- Other measures (if undertaken) to ensure study quality

Additional new submissions for these components will be made at a later date when they are ready.

## APPENDIX 1 – Detailed Description of the CVD Prevention and Management ‘Package’

The intervention package will be based upon the application of the core strategies described in the national clinical guidelines for hypertension and cardiovascular disease management in China, with adaptation to ensure the interventions are practical and affordable in rural China. Broadly the package will encourage the identification of a set of high-risk individuals and then seek to improve their clinical management through the application of simplified guidelines and a defined follow-up schedule. This will be achieved by training the primary care providers in the selected villages and supplying an automated electronic sphygmomanometer to each village clinic. The package also includes built-in performance evaluation and feedback mechanisms and a simple performance-based provider payment scheme.

The initial training of the village doctors is considered the beginning of the intervention. Identification and management of high-risk patients will be on a continual basis and last for 2 years (and hopefully will continue even after the end of the study). Therefore, the duration of intervention is 2 years.

*Identification of individuals at high cardiovascular risk* - The package will focus attention on patients considered at high cardiovascular risk on the basis of their falling into one of the following three groups, regardless of current medication use:

- Physician-diagnosed history of coronary heart disease, ischemic stroke, or hemorrhagic stroke, or
- Older age (50 years or older for men; 60 years or older for women – “50+/60+” hereafter) and having physician-diagnosed Type I or type II diabetes
- Older age (50+/60+) and SBP 160 mmHg

These individuals will be identified by training the primary care provider to take a brief medical history and measure blood pressure in all patients 50+/60+. This will be done opportunistically when patients visit the village healthcare clinics for any reason. In addition, the primary care providers will be encouraged to seek out all patients known to have previously suffered from cardiovascular disease using their knowledge of the community and the connections that they have within it. The more time-consuming and costly approach of screening all adults will not be done because it would not be sustainable.

Patients that fall into other groups defined for management under existing guidelines (such as patients with SBP < 160 but 140 mmHg or DBP < 100 but 90 mmHg) will be notified of their status and receive treatment but their management will not be specifically emphasized within this project. The rationale for this approach is that the interventions tested should be feasible for widespread rollout if they are proved effective and this would not be the case if every patient with an SBP of >140mmHg was to be offered long-term drug treatment.

*Management of individuals at high cardiovascular risk -* The intervention component of the program will train the primary care providers to:

- Give all high-risk patients lifestyle recommendations focusing on the consumption of a low-salt diet and smoking cessation;
- Measure blood pressure for every high-risk patient in every visit
- Prescribe evidence-based medications to high-risk patients, focusing on aspirin, diuretics, beta blockers, calcium antagonists, and ACEI/ARB, as appropriate;
- Implement a follow-up program amongst these patients with the goal of ensuring long-term adherence to the recommended interventions;
- Refer difficult to manage patients to the services provided by the township medical center.

The decision making process for patient management, follow-up and referral will be a central aspect of the primary care provider training and will be reinforced by various printed materials. The details of the proposed management algorithms are provided in Appendix 1-A. These flow charts will be re-designed and printed as large colored posters for village doctors to post on the wall of their clinics for easy reference. Explanations regarding the flow charts: the charts appear to be complex with some redundancy because they are designed 1) to separate the algorithm for screening and identification of high-risk patients from the management of different types of patients; 2) to clearly distinguish high-risk patients who will be recorded in the case management records from those who won’t; 3) to emphasize the fact that these patients need to be regularly followed up (like a management loop) instead of only a one-time visit; and 4) to be used as an easy-to-follow almost fool-proof process chart for clinical decision-making. Although the charts look complex, the hope is that once trained, the village doctors will be able to refer to the charts (and the technical manual) for most of their CVD-related clinical needs.

As part of the package, the primary care providers will be trained in the use of a patient-centered case management record that will be used to record relevant clinical indicators of risk, interventions and follow-up visit data. The village doctors will fill these records out manually and keep them in their clinics for each high-risk patient managed by them. The record will be designed as a 13-page printed booklet including the initial visit page and 12 identical pages for follow-up visits (a new booklet will be used for those who finish all 13 visits). The use of these records will not only improve the standardization and quality of clinical practices at the village level but will also be used to provide the basis for performance report and feedback. In addition, the information collected in these records will be used at the completion of the study to better understand the uptake of the package amongst the villagers. See Appendix 1-B for sample case management record.

The whole intervention package has 3 main integral parts: technical training, performance feedback, and provider payment.

